## ***14.2 Reporting Procedures:***

Adverse events will be recorded and reported to the Chief Investigator. The event will also be documented and discussed with all members of the research group in the research departmental meetings.

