### ***3.2 Supplementary Table S2: Details of adverse events experienced by participants in the PROMOTe trial.***

| No. | Adverse Event                          | Arm | Related to Study? |
|------------|-----------------------------------------------|------------|--------------------------|
| 1          | Bloated, loss of appetite, waist feels bigger | 2          | probably                 |
| 2          | Bloating                                      | 1          | probably                 |
| 3          | Bloating                                      | 1          | probably                 |
| 4          | Flatulence*                                   | 1          | probably                 |
| 5          | Wind                                          | 1          | probably                 |
| 6          | Constipation                                  | 1          | possibly                 |
| 7          | Diverticulitis                                | 1          | possibly                 |
| 8          | Cramps in legs                                | 1          | remote                   |
| 9          | Headaches                                     | 2          | remote                   |
| 10         | Hair loss*                                    | 1          | remote                   |
| 11         | Nose bleeds                                   | 1          | remote                   |

\*Experienced by same participant. Arm 1 = prebiotic. Arm 2 = placebo.

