## 10 Study design & Flowchart

### 10.1 Study Design

The proposed study will provide a simple but robust intervention study using protein supplementation and prebiotic food supplementation to improve our understanding of the mechanisms linking nutrition to health outcomes that are mediated by the gut microbiome.

The study will be a randomised, placebo controlled, double blinded, intervention study in which participants will be grouped into two different arms. Randomisation will control for equal distribution of key characteristics that may confound between group comparisons and will be assessed by analysis of pre-existing baseline data. Participants will be randomised as twin pairs, with one twin from the pair in the prebiotic food supplement arm and one twin from the pair in the placebo arm. Twin pairs are matched for age and often for sex, early environment, baseline genetic sequence, socioeconomic status etc., proving a strong model for detecting changes that are truly significant.

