the protein supplement plus prebiotic food supplement intake arm. After randomisation the supplements will be posted to the participant. Researchers and participants will be blinded as to which group each participant is in. The Kings Clinical Trials Unit will liaise directly with the company providing the supplements to ensure complete blinding of research team. A designated member of the departmental administration team will have access to the unblinded information.

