### **Examination:**

Measurements will be taken by the participant with a measuring tape provided in the postal pack. Participants will be asked to weight themselves if they have a weighing scales. Weighing scales can be calibrated using a standard household item, such as a tin of beans. Baseline Short Physical Performance Battery (SPPB) will be carried out remotely (this includes chair-rise time), with live instructions from a trained researcher. A dynamometer will be provided to all participants via post in order to measure handgrip strength, and this measurement will be taken with guidance from the trained researcher, during the video call. Any queries regarding the questionnaire, food diary, or cognitive assessment can be addressed.

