## **Stage 3: Dietary intervention**

Control and treatment arms: All participants will be provided with a sachet of powdered food supplement to be taken daily with a glass of water or other drink (hot or cold). All sachets will contain leucine-rich protein supplement.

Sachets for participants in the placebo arm will also contain 20 g of maltodextrin powder (placebo). Sachets for participants in the intervention arm will contain prebiotic food supplement. All participants will be asked to take 1 sachet daily, for a period of 12 weeks. These supplement sachets in each arm will be indistinguishable.

Regular contact will be made with participants by phone/email to encourage compliance and assess for any adverse effects. All participants will be encouraged to engage in regular resistance exercise at least twice per week throughout the intervention and will be provided with written advice on this at the beginning of the study.

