### ***14.1 Definitions***

**Adverse event (AE):** any untoward medical occurrence in a patient or study subject reported to the study team during in person and telephone visits.

**Serious adverse event (SAE):** any untoward and unexpected medical occurrence or event that;

1. Result in death
2. Is life threatening
3. Requires hospitalisation or prolongation of existing in-patient hospitalisation
4. Results in persistent or significant disability or incapacity

Medical judgement will be exercised in deciding whether an AE is serious. Important AEs that are not immediately life-threatening or do not result in death or hospitalisation but may jeopardise the subject or may require intervention to prevent one of the other outcomes listed in the definition above will also be considered serious.

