### ***Randomisation/Allocation Concealment/Blinding Procedures***

Participants will undergo computer generated block randomisation in twin pairs by the King's College London Clinical Trials Unit (KCTU). They will be randomised as twin pairs, with one twin in each arm. Researchers and participants will be blinded as to which arm each participant is in.

On completion of the data collection, the KCTU will issue a blinded list denoting what arm each participant is in (Arm 1; Arm 2), but without revealing which arm is the intervention and which the placebo, in order to facilitate blinded analysis to be carried out. Full unblinding will not take place until data analysis is complete. Until that point, only the KCTU will have access to the unblinded information.

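### Section 14.2 shares every adverse event with the whole research group, with no exception for outcome assessors; with co-twins in opposite arms, a gut symptom can suggest both allocations before the final test

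*Combined protocol and SAP*

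**What the plan says.** Protocol section 14.2 sends adverse events to the chief investigator and then adds: "The event will also be documented and discussed with all members of the research group in the research departmental meetings". Section 14.1 defines an adverse event as "any untoward medical occurrence in a patient or study subject reported to the study team during in person and telephone visits", so the rule covers minor symptoms as well as serious ones. Section 10.1, Stage 3, has symptoms sought while participants are still taking the sachets: "Regular contact will be made with participants by phone/email to encourage compliance and assess for any adverse effects". The flowchart in section 10.2 places telephone calls in weeks 3-5 and 7-9 and the final video call in week 12.

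Chair rise time is the primary outcome. Under Stage 2, Examination, the SPPB is done remotely ("this includes chair-rise time), with live instructions from a trained researcher"). Grip strength is taken under a researcher's guidance on the same call, and Stage 4 repeats the measures at the end of the study. Sections 10.1 and 12.3 state that researchers and participants are blinded. Section 10.1 splits every pair, "with one twin from the pair in the prebiotic food supplement arm and one twin from the pair in the placebo arm".

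On the allocation code, Stage 1 of section 10.1 says: "A designated member of the departmental administration team will have access to the unblinded information". The SAP section on randomisation, concealment and blinding says that full unblinding waits until the analysis is finished, and then: "Until that point, only the KCTU will have access to the unblinded information".

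**The concern.** Chair rise, SPPB and grip depend on effort, and a researcher instructs them in real time. If that researcher has formed a view of which twin is on the active product, the manner of instruction can differ between twins. The blinding promise exists to prevent this.

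Two features of the design make it worth attention. First, the sachets differ only in containing inulin and fructooligosaccharides or maltodextrin, and the stated aim is to change the gut microbiome. A team member who hears of bloating or wind could reasonably think of the prebiotic. Second, a guess about one twin is automatically a guess about the other. The primary model (SAP 7.2.1) takes twin pair as a random effect, so the comparison between co-twins is central to the result, and a guess would bear on both sides of it.

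The conflict over the code is a separate matter. If two documents name different holders, the trial cannot show who could have known the allocation.

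**Working it through.** The plan gives no figure on this point, so there is none to reproduce. The check is a reading of the route, followed by a count.

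**1. The route from event to assessor.**
- Which events: all of them (14.1, 14.2).
- Who hears: the whole group (14.2), with no carve-out for outcome staff, no de-identification and no delay.
- When events are sought: weeks 3-5 and 7-9 (10.2), before the week-12 test.
- Who tests: a trained researcher (10.1, Examination). No section separates this person from the callers or the meetings, and no check of blinding is described.

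The text therefore allows an assessor to hear of a participant's symptom before testing that participant.

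**2. How informative a gut symptom was.** Supplementary Table S2 lists 11 events, with the key "Experienced by same participant. Arm 1 = prebiotic. Arm 2 = placebo". I count nos. 1-7 as gastrointestinal: nos. 2-7 in arm 1 (6 events) and no. 1 in arm 2 (1 event).
- Share on prebiotic: 6/7 = 86%.
- Exact 95% lower limit: the p that solves 7p^6(1-p) + p^7 = 0.025, which is p = 0.42.
- Exact 95% upper limit: 1 - p^7 = 0.025, so p = 0.975^(1/7) = 0.996.
- Against guessing at random: P(6 or more of 7) = (7 + 1)/128 = 0.0625 one-sided, 0.125 two-sided.
- Fisher exact test on 6/36 v 1/36, one participant per event: p = 0.11.
- Bloating and gas only (nos. 1-5): 4 v 1, that is 80%, exact 95% CI 28% to 99%.

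**3. How far it could reach.** The footnote marks one participant with two events, and that person's other event was hair loss. The 7 gut events therefore come from up to 7 people. Supplementary Table S6 has 36 per arm, hence 36 pairs.
- Pairs: at most 7/36 = 19%.
- People: at most 14/72 = 19%.

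This is an upper limit. Two of the seven could be co-twins, and Table S2 has no dates, so some events may have come to light only after the final test. For the placebo event, a guess of prebiotic would have been wrong for both twins.

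**4. Cross-check.** The study-end bowel questionnaire (Supplementary Table S7) separates the arms weakly: diarrhoea 4 prebiotic v 2 placebo (p = 0.52), constipation 5 v 5 (p = 0.75).

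**5. Code holder.** Protocol 10.1 gives the unblinding information to one person in departmental administration. The SAP gives it to the trials unit alone until analysis is complete. Both statements cannot hold.

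**The case against.** Several points on the other side are sound.

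- A reader might infer that each gut event exposes two allocations. The documents do not support that. No code is disclosed in the meetings, one of the seven events was on placebo, and the interval around 86% includes 50%.
- Section 14.2 does not say that participants or pairs are named, or that discussion comes before the final visit. Both are permitted by the text rather than stated in it.
- The protocol lists no expected gastrointestinal effects of the prebiotic, and the split by arm in Table S2 was known only after unblinding. At the time, any link in an assessor's mind would have come from the nature of the product. The relatedness ratings fit such a link: all five bloating or gas events were rated probably related and all four non-gut events remote. The table does not show when those ratings were made.
- A reader might try to turn this into a bias in seconds by assuming how far encouragement shifts a pair. The documents give neither the size nor the direction of such a shift, and shifts in opposite directions would partly cancel. No such estimate should be quoted.
- Changing the meetings alone would not reach staff who take the adverse-event calls and may later run the test. The fix has to cover them.
- Team review of adverse events is a legitimate safety choice. The change should not weaken it.
- A reader might also infer that the administrator with the code deals with the twins. Section 10.1 names one person and gives that person no contact or outcome role. The enrolment and booking in section 12.1 come before the baseline visit, and randomisation follows that visit.

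What remains is that no written safeguard stands between case-level events and the assessor, and that the two documents contradict each other on the code.

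**Conclusion.** The point holds in a limited form. The plan promises blinded researchers, yet routes every adverse event to the whole group without shielding those who run the effort-dependent tests. Because pairs are split, a gut symptom can suggest both co-twins' allocations before the final test. The reach is at most 7 of 36 pairs (19%), with 6 of 7 gastrointestinal events on prebiotic (86%, exact 95% CI 42% to 99.6%).

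This rests on two assumptions that the text allows but does not state: that discussion identifies the participant or pair, and that it takes place before that participant's final test. The size of any bias in chair rise time cannot be derived from the documents, and nothing here shows that the primary result was biased. It is a cheap improvement that should be made. The contradiction over the code holder needs no inference and must be reconciled in any case.

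**What to change.** In protocol section 14.2 and the visit procedures:

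- Keep case-level discussion to the chief investigator and, where existing staffing allows, to staff who do not assess that participant.
- Until the participant's final test, give the wider group only de-identified summaries without twin-pair identity.
- Where existing staffing allows, have the week 3-5 and 7-9 calls made by someone other than that participant's final-visit assessor.
- At the final call, complete SPPB (with chair rise) and grip before asking about adverse effects.
- If one twin's code is broken, log the co-twin as unblinded too.

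Separately, make protocol section 10.1 (Stage 1) and the SAP blinding section name the same code holder, and state that this holder has no role in outcome collection.

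The cost is protocol wording and a change to the meeting agenda, with no extra staff. The downside is that fewer team members see individual events before the final visit. Safety oversight by the chief investigator and the sponsor is unchanged.

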### **11.2.1 Serious AEs:**

All SAEs (both related and unrelated) will be recorded and reported immediately to the chief investigator and the sponsor. Relapse and death due to an unrelated or pre-existing condition, and hospitalisation for treatment of a pre-existing condition do not require reporting as SAEs.

All SAEs should be reported to the research ethics committee (REC) within 15 days of the chief investigator becoming aware where in the opinion of the Chief Investigator, the event was:

Related i.e. resulted from administration of any of the research procedures

Unexpected i.e. an event that is not listed in the protocol as an expected occurrence.

The SAE report form for non-CTIMPs will be used (available from NRES website) and will be sent to the main REC for the trial.

### **11.2.3 Responsibilities**

The co-sponsors (King's College London and GSTFT) has delegated responsibility for the study to the chief investigator. The principal investigator at each site is responsible for reviewing all AEs and recording them appropriately in the study database.

## ***14.3 Ethics & Regulatory Approvals:***

This interventional study will be conducted in compliance with the principles of the Declaration of Helsinki (1996), the principles of GCP and in accordance with all applicable regulatory requirements including (but not limited to) the Research Governance Framework. The study may be subject to inspection and audit by King's College London and Guy's and St Thomas' NHS Foundation Trust under their remit as sponsors and by other regulatory bodies. This is to ensure adherence to GCP and the NHS Research Governance Framework for Health and Social Care (2nd edition).

This protocol and all related documents will be submitted for review to a Research Ethics Committee (REC). Any amendments to approved documents or newly created documents will likewise be submitted for approval. The study will be submitted for consideration for adoption on to the National Institutes for Health Research (NIHR) Clinical Research Network portfolio.

This study has been presented to the Department of Twin Research Volunteer Advisory Panel (VAP), who were in favour of it, and the documents have been reviewed by the eVAP, another group of volunteers who review materials remotely. The eVAP were also in favour of the study.

## **15 Compliance and withdrawal**

### ***15.1 Subject compliance***

Regular monitoring of compliance will be achieved by regular contact with the participants either via email, text messaging, or telephone. Compliance will be judged by completion of the end of study questionnaires and by the remaining number of sachets at the end of the study. Twin pairs will be advised not to share each other's supplements.

### ***15.2 Withdrawal / dropout of subjects***

Participants can withdraw their consent, without giving any reason at any time during the study by contacting the study contacts. Similarly, the participant can withdraw their consent for the continued retention and use of their samples even after they have been collected, without giving a reason. Reason for discontinuation from the study will be asked about sensitively and recorded. If a subject withdraws consent to the use of donated biological samples, the retained samples will be disposed of/destroyed.

If a participant, who has given informed consent, loses capacity to consent during the study, the participant would be withdrawn from the study. Identifiable data or tissue already collected with consent would be retained and used in the study. No further data or tissue would be collected, or any other research procedures carried out on or in relation to the participant.

The Chief Investigator:

- Will ensure subjects' withdrawal of informed consent is notified immediately to Guy's and St Thomas' NHS Foundation Trust and King's College London.
- Will ensure that biological samples from that subject, if stored at the study site, are immediately identified, disposed of/destroyed and the action documented.
- Will ensure that the laboratory(ies) holding the samples is/are informed about the withdrawn consent immediately and that samples are disposed of/destroyed and the action documented and returned to the study site.

Guy's and St Thomas' NHS Foundation Trust and the King's College London will ensure that the central laboratory(ies) holding the samples is/are informed about the withdrawn consent immediately and that samples are disposed of/destroyed and the action documented returned to the study site. In the event that analysis/research has already been performed, Guy's and St Thomas' NHS Foundation Trust and King's College London will retain the results and associated data for regulatory reasons but individual data that can be identified as originating from that subject will not be used in any subsequent analyses.

## 16 Data

### *16.1 Data handling and record keeping*

The Chief Investigator will act as custodian for the study data. The following guidelines will be strictly adhered to:

(1) Completed paper case report forms should be stored within the study site file.

IRAS project ID: 257415 Version 1.0

(2) The study site file will be located in a locked storage with access restricted to permitted research staff.

(3) All study data will be stored and archived in line with the Medicines for Human Use (Clinical Trials) Amended Regulations 2006.

## 17 Statistical considerations

### *17.1 Sample size calculation*

From our existing data, we have observed that chair-rise time is to a good approximation log normal, with  $\log_{10}(\text{time})$  having a SD of 0.126. We consider a relative reduction in average time of 20% to be both clinically important and plausible. Based on these figures, we would need complete data on 30 subjects per group (60 in total) for 80% power. Allowing for 20% dropouts, we would need 70 (35 per group) recruited. Based on the numbers we plan to recruit for the study, we estimate a recruitment time period of 18 months.

We have estimated a powered sample size based on other studies using chair-rise time, however we note that no study has looked at this in the context of protein and/or prebiotic food supplementation and therefore may not be accurate.

### *17.2 Statistical analysis*

Analysis will assess microbiota differences between the two study arms and between twin pairs. Microbiome composition will be analysed with respect to (1) species diversity, (2) compositional differences, and (3) differences in abundance of taxa. Analysis will be carried out using statistical programs STATA and RStudio. All analysis will take a hierarchical approach; crude models assessing just the variable of interest (prebiotic supplementation), and models adjusted for key biological (age, gender, exercise etc..) and technical covariates (e.g. differences in library size) will be applied.

Differences in species diversity and richness will be compared between each study arm in regression analysis in crude and adjusted models. Distance matrixes characterise the inter-individual differences in microbiota composition; ordination analyses and permutational multivariate analysis of variance (PERMANOVA) will be used to understand differences in composition between each study arm.

ASVs will be collapsed to family, order, and phylum levels, with hierarchical models, adjusted for each potential mediator individually, then fully adjusted. All models will be adjusted for multiple testing.

All twins within each study arm will be used in paired tests to assess if microbiota dissimilarity increased with differences in muscle strength, taking relevant covariates into consideration. An intention to treat analysis will be carried out to address participants who do not complete the study.

Secondary analyses will include linear mixed effects regression models to investigate associations between microbiota composition, microbial metabolite markers, markers of appetite and other lifestyle and physiological parameters including muscle strength (as measured by chair-rise time) adjusting for covariates and multiple testing.

